### 5.3.2. Evaluation of the causality of adverse events

The investigator should use his or her knowledge of the patient, the circumstances surrounding the event, and an assessment of any other potential causes to determine whether the adverse event is considered to be related to the study MD or the investigative procedure.

The following guidelines should be considered:

- Temporal relationship between the onset of the event and the first use of the MD under study

- Course of the event, with particular attention to the effects of discontinuing the study MD or reintroducing the study MD (if applicable)
- Known mechanism of action at the MD
- Body site or organ that may or may not be affected by the MD or condition
- Known association of the event with the investigational MD or similar devices
- Known association of the event with the disease under study
- Presence of risk factors in the patient or use of concomitant medications known to increase the frequency of the event
- Presence of factors unrelated to the MD that are known to be associated with the occurrence of the event.

Causality of MDs according to MDCG 2020-10/1 page 9

|             |                                                                                                                                                                                                                                                                                                                                                         |
|-------------|---------------------------------------------------------------------------------------------------------------------------------------------------------------------------------------------------------------------------------------------------------------------------------------------------------------------------------------------------------|
| Not related | Causality with the MD, comparator or procedures can be excluded                                                                                                                                                                                                                                                                                         |
| Possible    | Causality with the use of the MD, comparator, or CI procedures is weak but cannot be completely ruled out. Other causes are also possible (underlying or concomitant disease/clinical condition/effect of another treatment). Cases where the relationship cannot be assessed or no information has been obtained should also be classified as possible |
| Probable    | The causal link to the use of the MD or comparator, or the relationship to the CI procedures, appears relevant and/or the event cannot be reasonably explained by another cause                                                                                                                                                                         |
| Some        | The serious adverse event is related to the use of the MD, comparator, or trial procedures beyond a reasonable doubt.                                                                                                                                                                                                                                   |

The categories "possible", "probable" and "certain" correspond to a proven or reasonably foreseeable causal link.

In cases where no information is available to define the causal link, fill in

The default setting is "possible".

### **5.3.3. Evaluation and Reporting of Serious Adverse Events and Incidents**

The regulations have instituted a different notification circuit depending on whether an event/incident is suspected to be related to the MD itself or to the investigation procedure.

[figure not shown]

a. **Incidents (or risks of incidents) that may be related to the medical device (MD)**

They must be notified by the investigator to the **local materialovigilance correspondent of the institution in which the study is being carried out**, without delay and as soon as he becomes aware of them. **They follow the standard materialovigilance circuit of the institution, under the responsibility of the investigator (care circuit).**

The form dedicated to material safety is not to be sent to the sponsor, the mention of these AEs/incidents in the eCRF table being sufficient. The investigator should indicate in the eCRF that the transmission has been made to the local correspondent, via the checkbox in the table of AEs/Incidents.

The sponsor ensures that the required notifications have been made to the local Material Safety Correspondents of the investigating centers.

b. **Serious adverse events** in relation to **the investigation procedure that precedes it** according to the investigator

The investigator must report to the sponsor, without delay and at the latest **within 3 calendar days from the** day he/she becomes aware of them, all serious adverse events of the investigation procedure that preceded them that occurred in the study.

This initial notification should be followed by a detailed follow-up. The investigator must document the event as well as possible (thanks to copies of laboratory results, test reports and/or hospitalization reports giving information on the serious event, including relevant negative results, **without omitting to make these documents anonymous** and to write down: acronym of the research, number and initials of the patient, the medical diagnosis and establish **a causal link** between the serious adverse event and the medical device(s) and the action taken to implement it) **and, if possible, give the medical diagnosis.**

The investigator will complete and sign the paper SAE notification form and send the scanned form by email to [REDACTED]. He/she should specify in the subject line "NAME OF THE STUDY-Patient-Center".

**The investigator follows any serious adverse event until complete resolution** (disappearance of signs and symptoms), or consolidation (return to a medically acceptable state) even if the patient has stopped the research procedure, **and communicates to the sponsor any additional information** concerning this event by means of follow-up reports.

### 5.3.4. Procedures and deadlines for notifying the sponsor

The investigator notifies the sponsor of events as defined below:

| TYPE OF EVENT                                                                                       | METHODS OF NOTIFICATION                                                                                           | NOTIFICATION DEADLINE                                                                                                      |
|-----------------------------------------------------------------------------------------------------|-------------------------------------------------------------------------------------------------------------------|----------------------------------------------------------------------------------------------------------------------------|
| Event of interest                                                                            | Collection in the e-CRF (AE table)                                                                                | Without delay
as soon as you are aware of it,
and at the latest within 3 calendar days                 |
| Non-serious adverse event Suspected of being related to the clinical investigation procedure | Collection in the e-CRF (AE table)                                                                                | As soon as you are aware of it                                                                                             |
| Serious adverse event Suspected of being related to the clinical investigation procedure     | Collection in the e-CRF (AE table)
+ Initial SAE form
+ Follow up if necessary
By mail                   | Without delay to the Sponsor,
as soon as you are aware of it,
and at the latest within 3 calendar days |
| New Fact                                                                                     | By email                                                                                                          | Without delay to the Sponsor,
as soon as you are aware of it,
and at the latest within 3 calendar days |
| Incidents (MD)                                                                               | Collection in the e-CRF (AE table) + checkbox in the eCRF (AE table)
+
Materialovigilance declaration form  | Without delay to the local materialovigilance correspondent, as soon as he is aware of                              |
| Special situation                                                                            | SIP form to be completed +
Follow up if necessary
By email

+ check box in the eCRF (Deviation table) | Without delay
(Max 24 hours)
to the Sponsor                                                            |

### 5.3.5. Notification period to the sponsor

[figure not shown]

\*Consent see details in § 7.8

The investigator is responsible for recording on the e-CRF and notifying the sponsor of the events listed in 5.3 of this protocol, occurring during the entire study:

- From 1ère administration of the study MD until discharge from the ICU or D28 if the patient is still in the ICU at D28.

Each event will be followed until complete resolution (stabilization at a level deemed acceptable by the investigator or return to the previous state), even if the patient is withdrawn from the study.

Special case - after completion of the study:

The sponsor should be informed if the investigator becomes aware of a serious adverse event that occurred after the end of the registration period and reporting of SAE period, without time limitation and without delay, when the SAE is likely to be related to the investigative procedure.

These events must be reported using the Serious Adverse Event Reporting Form by sending paper forms by email to the following address: [REDACTED]

## 5.4. ROLE OF THE SPONSOR

### 5.4.1. Events to record

The sponsor records:

- any adverse event defined in the protocol as critical to the evaluation of the study outcome
- any serious adverse event related to the investigation procedure

c) any incident of a MD (only nature, start date, end date, severity, causality, action taken and evolution)

d) any new element concerning an event referred to in (a) to (c).

The sponsor is responsible for the ongoing evaluation of the safety of the investigative procedure.

The sponsor should verify the content, consistency of SAEs and assess:

- The causal relationship (unrelated, possible, probable, certain) between the serious adverse event and the investigative procedure,
- The expected or unanticipated nature of serious adverse events in the investigation procedure.

In the event of a different assessment by the sponsor and the investigator, both opinions are mentioned on the declaration sent to the competent authority if such a declaration is necessary.

Without prejudice to this centralized evaluation, the sponsor monitors the occurrence of MD-related complications in the context of its research via the AE/Incident table.

#### 5.4.2. Declaration to the Competent Authority

The sponsor must report to the Competent Authority "**reportable events**"; **any serious adverse event** with a proven or reasonably foreseeable causal link (possible, probable, certain) with the investigation procedure, the new facts and, if applicable, the measures taken, as from the day on which it becomes aware of them. Only causality level 1 (i.e. "unrelated") is excluded from reporting. Deadlines for reporting by the sponsor to the ANSM :

| Type of event                                                                                                                                                                     | Time limit for initial declaration / Follow up                          |
|-----------------------------------------------------------------------------------------------------------------------------------------------------------------------------------|-------------------------------------------------------------------------|
| New fact                                                                                                                                                                          | WITHOUT DELAY                                                    |
| A "reportable" event (SAE) that has resulted in death, imminent risk of death, serious injury or illness and requires prompt corrective action or new information on these cases. | WITHOUT DELAY and at the latest within 2 calendar days* . |

|                                                                                                                                                                                          |                                                                         |
|------------------------------------------------------------------------------------------------------------------------------------------------------------------------------------------|-------------------------------------------------------------------------|
| This includes relevant and unexpected events when they become a potential public health hazard. It also includes the possibility of multiple deaths occurring at short intervals. |                                                                         |
| Other "deferrable" events and any new information relating to these events                                                                                                               | WITHOUT DELAY and at the latest within 7 calendar days* . |

\* from the moment of taking cognizance

## **5.6. *INDEPENDENT SAFETY COMMITTEE (ISC)***

The ISC is an advisory committee responsible for advising the sponsor and the study coordinator on the safety of a clinical trial. Its members are competent in the field of clinical trials (pathology, safety and ethics) and are not involved in the study. They are appointed for the remainder of the study and are committed to their participation as well as to respecting the confidentiality of the data. The choice of the members of the ISC is made in a collegial manner by the coordinator and the sponsor.

Within the framework of this study, a ISC is constituted after the start of the study following a New Safety Fact declaration transmitted to the ANSM on 22/11/2021.

### **Role:**

- Monitor the progress of the study, the characteristics of the patients included and the frequency of events of particular interest (self-extubations and repositioning of the endotracheal tube).
- Provide an advisory opinion on whether the trial should continue.
- The CIS is also notified of all security information transmitted to the appropriate authorities.

### **Operating procedures**

The committee met in June 2022 and reported its findings before the beginning of the second period. In order to meet these deadlines, only the data from the first 300 included patients

were presented to the committee.

The committee decided to continue the study without any restrictions.

It may also meet at the request of the sponsor in the event of safety problems reported by the investigators during the study.

The committee shall inform the coordinator and the sponsor in writing of its findings.

The CIS will not have access to data concerning the primary endpoint (peri-oral lesions). No statistical tests will be performed, only descriptive data will be presented.

In case of a tendency to over-morbidity, a temporary suspension or a final decision of the research will be taken during a meeting organized by the coordinator, the different investigators and the members of the CIS.

## **6. DATA MANAGEMENT AND STATISTICS**

### **6.1. COLLECTION AND PROCESSING OF STUDY DATA**

#### **6.1.1. Data collection**

One electronic case report form (eCRF) will be created per patient. All information required by the protocol must be provided in the eCRF. It should include the data needed to confirm compliance with the protocol and all data needed for statistical analyses; it should identify major deviations from the protocol.

The person(s) responsible for completing the CRFs/eCRFs (investigator, CRA, etc.) must / (s) must be defined and is/are identified in the delegation of responsibilities table for each center (kept in the investigator's binder).

#### **6.1.2. Data coding**

By signing this protocol, the principal investigator and all co-investigators agree to keep confidential the identities of the patients who participated in the study.

The transmission of a person's data for research purposes will therefore only be possible if a coding system is applied; the presentation of the research results must exclude any direct or indirect identification.

The identification of patients will be done according to the order of inclusion of patients by a number automatically assigned by the Clinsight software (eCRF) then completed by the initials of the patients (1st letter of the first name + 1st letter of the last name).

This code will be the only information that will appear on the eCRF notebook and will allow the eCRF to be linked to the patient afterwards.

The investigator is also required to code the patient data on all documents that he/she may have in his/her possession (reports of imaging or biological examinations, etc.) that are attached to the eCRF.

A correspondence table will be set up at the participating center. This table will be kept in a secure place by the principal investigator of the center and will contain the patient code and his nominative data in order to be able to go back to the patient file in case of missing or erroneous data. No clinical data will be collected in these correspondence tables.

### **6.1.3. Data processing**

The collection of clinical data will be based on the implementation of a database and the creation of data entry masks similar to the observation book in accordance with the protocol and regulations currently in force.

## **6.2. STATISTICS**

[name]

CHD La Roche Sur Yon

The analyses will be carried out using the R software version 3.5.1

### **6.2.1. Description of methods statistics planned including schedule of planned interim analyses**

The statistical analysis report will be written according to the recommendations proposed by Arnup et Al (13) on cross-over cluster trials.

#### **Baseline features**

A descriptive analysis of the clusters and patients will be presented for each of the 2 periods according to the sequence (cord fixation then adhesive strips // adhesive strips fixation then cord).

The description will include the numbers and percentages of terms for categorical variables and the minimum, maximum, mean, standard deviation and median for quantitative variables.

### **Analysis of the assessment criteria**

To account for the study design, all criteria (primary and secondary) will be compared using hierarchical generalized linear models. The type of fixation, the period and the center (=cluster) will be taken into account in the model as fixed effects; the center\*period interaction will be taken into account as a random effect (14).

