#### Main criterion

The percentage of patients with at least one peri-oral lesion will be estimated with a 95% confidence interval for both types of fixation. A logistic regression model taking into account the duration of the patient's endotracheal tube retention and the study design will be applied.

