### **6.2.2. Statistical justification of the number of inclusions**

The study will take place in 16 centers (clusters) over two 12-month periods.

According to the IDEFIX study (7), we hypothesize that 35% of patients with a "cord and sleeve" fixation system have a peri-oral lesion compared to 20% with the elastic adhesive tape system.

The calculation of the number of subjects needed must take into account the design of the study and thus the two intra-class and inter-class correlation coefficients (15)

As we have no data on the estimation of correlation coefficients, we have retained, for the calculation of the number of subjects, a "moderate" intra-class correlation coefficient and therefore defined at 0.1, and as recommended, an inter-class correlation coefficient equal to half of the intra-class correlation coefficient, i.e. 0.05 (16)

With 90% power and 5% alpha risk, we calculated that each of the 16 centers would need to include an average of 24 patients per period.

A total of 768 patients are to be included.

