### **6.2.3. Expected level of statistical significance**

The alpha risk is set at 5%.

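### Primary endpoint: with centre as a fixed effect, an ordinary maximum-likelihood fit of the stated mixed model rejects a true null about 16–17% of the time at the planned correlations, so the estimator and a 14-df reference should be fixed

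*Protocol*

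**What the plan says.** Section 6.2.1 of the protocol (Analysis of the assessment criteria) uses hierarchical generalized linear models and sets one structure for all criteria: "The type of fixation, the period and the center (=cluster) will be taken into account in the model as fixed effects". The centre-by-period interaction is the only random effect. For the primary endpoint the paragraph on the main criterion adds: "A logistic regression model taking into account the duration of the patient's endotracheal tube retention and the study design will be applied".

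Section 6.2.2 plans 16 centres, two periods and on average 24 patients per centre and period, 768 in total. It assumes lesion rates of 35% and 20%, a moderate "intra-class correlation coefficient and therefore defined at 0.1", and "an inter-class correlation coefficient equal to half of the intra-class correlation coefficient, i.e. 0.05". These values are assumptions, introduced with the words "As we have no data on the estimation of correlation coefficients". The target is stated as "With 90% power and 5% alpha risk", and section 6.2.3 repeats the 5% level.

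Section 6.2 names R 3.5.1 as the software. The protocol does not name an estimation method, a test statistic or a small-sample reference distribution.

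**The concern.** Within a period every patient in a centre gets the same fixation system. Fixation therefore varies only between the 32 centre-period cells, and the precision of its effect depends on the centre-by-period variance. In the stated model that variance has to be estimated after 18 fixed parameters have been fitted to those cells. Maximum likelihood makes no allowance for fitted parameters. With more than half of the cell-level information spent on them, it pulls the variance towards zero. The fit then behaves much like ordinary logistic regression with centre indicators, the standard error of the fixation effect is too small, and the confidence interval is too narrow.

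At stake is the type I error of the primary test. The sample size allows for between-period variation within centres, and the analysis could largely lose sight of it.

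**Working it through.** **Inputs (sections 6.2.1 to 6.2.3).** 16 centres, 2 periods, m = 24 per cell; rates 35% and 20% (mean 27.5%); correlations ρ = 0.10 within a period and η = 0.05 between periods; alpha 5% (taken as two-sided) and power 90%.

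**1. The plan's own figure.** Individually randomised n per arm, unpooled variance: (1.960 + 1.282)² × (0.35×0.65 + 0.20×0.80) / 0.15² = 10.507 × 0.3875 / 0.0225 = 181. The cluster-crossover design effect is 1 + (m − 1)×0.10 − m×0.05 = 0.90 + 0.05m. Solving 16m = 181 × (0.90 + 0.05m) gives m = 162.9 / 6.95 = 23.4, so 24 per cell (design effect 2.10) and 16 × 2 × 24 = 768. The plan's numbers reproduce.

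**2. Parameter count.** Intercept 1 + fixation 1 + period 1 + centre contrasts 15 = 18. From 32 cells, 32 − 18 = 14 df remain.

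**3. Why maximum likelihood fails here (linear approximation).** In units of the outcome variance:
- binomial part of a cell mean: w = 0.90/24 = 0.0375;
- centre-by-period part: 0.10 − 0.05 = 0.05;
- total: V = 0.0875, so w/V = 42.9%.

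Maximum likelihood divides the residual sum of squares by 32, so its expectation is 14/32 = 43.75% of V. That is almost exactly the binomial floor of 42.9%, and the interaction variance is estimated as zero whenever χ²(14) < 32 × 0.429 = 13.7, which has probability 53%.

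The test statistic is Z × √(V / V̂), with V̂ = max(w, V·χ²(14)/d). Here d = 32 for maximum likelihood with centre fixed, d = 14 for restricted likelihood, and d ≈ 16 for maximum likelihood with centre random. Integrating over χ²(14) at 0.10/0.05:

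| Fit | z | t on 14 df |
|---|---|---|
| Centre fixed, maximum likelihood | 17.3% | 13.7% |
| Centre random, maximum likelihood | 8.5% | 6.2% |
| Centre fixed, restricted likelihood | 6.9% | 4.9% |

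**4. Logistic simulation.** No true effect, 24 per cell, rate 27.5%, and logit-normal centre and centre-by-period effects calibrated to 0.10/0.05 (variances 0.303 and 0.290 on the logit scale). There were 2,000 trials per run unless stated, with simulation error of about 0.8 points near 16%.

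| Analysis | Rejection at nominal 5% |
|---|---|
| Stated model, maximum likelihood, Wald z (two separate simulations) | 16.4% and 17.2% |
| Stated model, maximum likelihood, likelihood ratio | about 16% |
| Stated model, maximum likelihood, t on 14 df | about 13% |
| Centre random, maximum likelihood, z | 8.2–8.3% |
| Centre random, maximum likelihood, t on 14 df | 6.0–6.3% |
| Centre fixed, restricted-likelihood-type, z | 4.5% (300 runs, 97% converged) and 6.8% |
| Centre fixed, restricted-likelihood-type, t on 14 df | 3.1% and 4.8% (same two fits) |
| Centre-level t test, 14 df | 4.7–5.0% |

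Under maximum likelihood the interaction variance was about zero in 57% of trials, and the mean standard error was 0.184 against an empirical 0.265.

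**5. Sensitivity (stated model, maximum likelihood, z).** Rates of 20% and 35% both give 16.6%. Unequal centre sizes (assumed coefficient of variation 0.4) give 18.7%. Correlations of 0.05/0.025 give about 12%, 0.10/0.08 about 11% (linear approximation), and 0.02/0.01 between 7% and 8%.

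**The case against.** The strongest reply is that the protocol never says maximum likelihood. It names a model class and R, but no package, function, estimator or test, and the fixed-centre structure holds close to 5% under a restricted-likelihood-type fit. Estimator and degrees of freedom are also details often left to an analysis plan, which is not at hand. The correlations are assumed, and at smaller values the excess shrinks. The protocol cites a methods paper on cluster-crossover trials with binary outcomes for this structure, and its advice cannot be checked here.

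Most of this stands and limits the claim. A reader might infer that the stated model by itself yields a 17% error. The documents do not support that, because the figure depends on an estimator that they leave open. A reader might also blame the fixed centre alone, but making centre random under maximum likelihood still leaves about 8% with z.

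The reply does not dispose of the point. The protocol does fix the structure, and that structure makes the choice of estimator decisive. Maximum likelihood is the usual fit for a logistic mixed model, and nothing in section 6.2 steers the analyst away from it. A degrees-of-freedom rule alone would not repair the test, since t on 14 df still gives about 13–14%.

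**Conclusion.** The point holds conditionally, for the binary primary endpoint. If the stated model is fitted by maximum likelihood with a Wald z or likelihood-ratio test, the nominal 5% test rejects a true null about 16–17% of the time at the plan's assumed correlations. It exceeded 5% at every correlation pair tried. A restricted-likelihood-type fit brings the rate to about 4.5–7% with z and 3–5% with t on 14 df.

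The calculation assumes logit-normal centre and centre-by-period effects and, except where stated, equal cells of 24. It omits the intubation-duration covariate, for which the protocol gives no figures.

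Two further inferences should be resisted. First, the protocol gives the same structure to the secondary criteria, but no error rate was worked out for the Poisson, ordinal, survival or linear analyses, so these figures should not be read across to them. Second, the 90% power in section 6.2.2 is not a product of an oversized test. It comes from a design-effect calculation that reproduces and is unaffected.

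**What to change.** In section 6.2.1, for the primary analysis, state the estimator and the reference distribution. Two options are acceptable:

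- Keep centre, period and fixation fixed and centre-by-period random, require a restricted-likelihood-type fit, and refer the fixation effect to t on 14 df (about 3–5%).
- Make centre random alongside centre-by-period, keep period and fixation fixed, and refer the fixation effect to t on 14 df (about 6%).

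In either case add a confirmatory centre-level analysis: the within-centre difference in lesion proportion between periods, compared between the two sequences by t test on 14 df (about 5%).

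This changes wording only, with no effect on data collection or sample size. The price is a wider, correctly sized confidence interval. The restricted-likelihood fit may also occasionally fail to converge (about 3% of simulated trials), so the text should say that the centre-level result is used in that event.
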